#### Randomisation

The hospitals participating in the trial are divided into strata. For each stratum random block randomisation is performed in blocks of 4–6. Within these blocks patients are randomly assigned to either the SoC alone or intervention + SoC arm in a 1:1 ratio. Results on randomisation are communicated to the health care providers.

#### Blinding

The measurements performed to determine non-adherence are only reported to the health care providers when patients ware randomised to the intervention + SoC arm. Measurements from the control arm are only available after completion or withdrawal of the study. Also, the laboratory that performed the measurements are not aware of the randomisation or which ID belonged to which patient. Only the coordinating researcher is not blinded and thereby is able to report the results from the intervention + SoC arm patients to the right physician. The coordinating researcher does not perform the actual intervention.

#### Standard of care (SoC) alone

SoC includes visits at 3 (t3), 6 (t6), and 12 (t12) months follow-up, with preferably a 24-h ABPM, and otherwise an automated office blood pressure (AOBP) combined with DBS sampling. In the SoC arm the results on drug concentrations are not reported during the study and are only used for resarch purposes.

The results of the blood pressure measurements are available for all healthcare providers. If deemed necessary by the treating physician it is allowed to schedule extra appointments outside the research visits. Also, it is allowed to make changes to the AHD treatment during every visit, without restriction with regard to the choice or dose of drugs. These changes are registered at every visit. If a patient switched to AHDs that are not included in the TDM method, only blood pressure measurements are included in the analysis.

Patients are allowed to make life style changes during the trial. These life style changes can possibly influence the adherence outcome and is therefore taken into account in our power calculation.

#### Intervention + SoC

The intervention can be described as a ‘comprehensive personalised feedback conversation’ added to SoC, and consists of a three-step method [27]. For this comprehensive converstation extra consultation time was planned for phycisians that usually only have 10-min consultations. When patients are going to a nurse practioner for blood pressure control, no extra time will be planned while they already have 30-min consultations.

First, results of the AHD concentrations measured with UPLC-MS/MS are reported back to the healthcare provider.

In the second step of the intervention, the treating physician or nurse practitioner have to relay the findings of the drug concentrations in a non-accusatory way. To support and guide exploration of reasons for non-adherence a communication tool is developed by a sociologist and psychologist as previously discribed by Peeters et al [27]. By examining the reasons for non-adherence, tailored solutions can be agreed upon. Therefore, in the final step, based on the individualised determinants of adherence and potential solutions, a plan is made to improve adherence to AHDs.

All health care providers have to follow a training beforehand to improve their communication skills. This training includes a 90 min lecture on the theory around adherence and how to improve this with communication. After the lecture, participants have one hour to practice the feedback conversation with one another, coached by a sociologist or psychologist. Also, a digitial version of the training is available as a booster.

Patients in the intervention + SoC arm receive personalised feedback at t0 and t3. At t6 and t12 results on drug concentrations are still reported to the treating health care providers, but not communicated to the patient to determine sustainability of the earlier intervention (Fig. 1).

### Methods of measurement

#### Blood pressure measurement

24-h blood pressure is recorded with the available ABPM device on site. All devices have to be approved for use in clinical practice. Measurements are performed with the device attached to the non-dominant arm if possible. Patients are instructed to relax their arm during the measurements and to pursue their normal daily activities. During the 24-ABPM patients are also asked to write down physical and stressful activities in a diary, as well as their true sleeping times. Depending on the hospital, BP is measured at a 20-min or 30-min interval during daytime and a 30-min or 60-min interval at night-time. Measurements are included if > 50% of the 24-h measurements was successful which includes at least 20 valid awake measurements and 7 valid asleep measurements [28, 29]. If a patient is eligible for the study because of a 24-h ABPM ≥ 135 and/or 85 mmHg measured for clinical purposes and the fingerprick is obtained within 4 weeks after this measurement, it is a allowed to use this ABPM measurement as inclusion criterion. However, an AOBP has to be performed at time of the fingerprick and needs to be ≥ 140 and/or 90 mmHg. If a patient does not want to do a 24-ABPM during the eligibility visit, they are excluded from participation. At all the follow-up visits, the 24-h ABPM can be replaced with a 30-min AOBP upon reasonable request of the patient as stated before.

#### Adherence

Two validated UPLC-MS/MS methods combined with a DBS sampling method are used to determine non-adherence to the aforementioned AHDs up until 24 h after intake of the drug [25, 26].

Sampling has to be performed by trained healthcare providers or researchers, but on occasion also by study subjects themselves after an oral and written instruction. Sampling is performed by means of a blood lancet (BD microtainer 2.0 mm × 1.5 mm) and filter papers (Whatman™, protein saver, 903 card). Five drops of blood need to be sampled per patient per time point of which at least one is needed for analysis. Each drop sampled on the paper has to be at least 6 mm in diameter to assure accurate measurement. The patient is asked to estimate the time of intake of the AHDs and time of sampling will be registered by the researchers. Samples are sent by mail in a paper envelope containing a lab form with information on the sample and a moisture absorber bag. Measurements of drug concentrations in the lab are performed every two weeks to assure minimal degradation of the drugs. Furthermore, outcomes of the drug concentrations have to be reported in time to the health care providers of the patients randomised to the intervention + SoC arm.

The adherence of patients is determined by means of the absence [< lower limit of detection (LLOD)] or presence of all the expected drugs in blood (Table 1). Expected drugs are drugs that were prescribed and measurable with the previously validated DBS method [25, 26]. When none of the expected drugs are detected in the patient’s blood, the patient is scored as non-adherent. Furthermore, when one or more, but not all drugs are absent from blood, the patient is scored as partially non-adherent. When all expected drugs are found, the patient will be considered adherent.

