#### Secondary objectives

Secondary endpoints include the effect of the intervention on the proportion of patients adherent to AHDs and patients fulfilling the definition of RH over time including baseline (t0), t3, t6 and t12.

Furthermore, the number of required AHDs as well as the defined daily dose (DDD) is calculated at t0 and t12 in both arms to determine if there is a difference over time between the arms.

Lastly, the cost-utility of the intervention vs standard of care in resistant hypertension is determined.

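### Stopping an undetected drug can turn a patient 'adherent' without any change in pill-taking, and only intervention-arm prescribers can do this knowingly

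*Protocol article*

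**What the plan says.** All references are to the protocol article.

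- **Scoring (Adherence).** The reference list is defined thus: "Expected drugs are drugs that were prescribed and measurable with the previously validated DBS method". The rule for success is all-or-none: "When all expected drugs are found, the patient will be considered adherent". The intermediate class is also fixed: "when one or more, but not all drugs are absent from blood, the patient is scored as partially non-adherent". Nothing ties the list to the t0 regimen, and nothing says how a drug stopped during follow-up is scored.
- **Regimen changes (Standard of care (SoC) alone).** Here "it is allowed to make changes to the AHD treatment during every visit, without restriction with regard to the choice or dose of drugs". Because the intervention is added to SoC, the same freedom applies in both arms. On recording: "These changes are registered at every visit". The only scoring rule for a changed regimen concerns a switch to drugs outside the assay, after which only blood pressure is analysed.
- **Who sees the drug results (Blinding; SoC alone; Intervention + SoC).** "The measurements performed to determine non-adherence are only reported to the health care providers when patients ware randomised to the intervention + SoC arm". For the control arm: "In the SoC arm the results on drug concentrations are not reported during the study". Intervention-arm providers receive results at t0 and t3 for the feedback conversation, and still receive them at t6 and t12.
- **Endpoint and test (Secondary objectives; Statistical analysis).** A secondary endpoint is "the effect of the intervention on the proportion of patients adherent to AHDs", at t0, t3, t6 and t12. Change in non-adherence is compared between arms by a chi-square test.

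**The concern.** The score has a numerator set by the patient (drugs found) and a reference list set by the prescriber (drugs expected). A patient can therefore move from partially non-adherent to adherent in two ways: by starting to take the missing drug, or by having that drug removed from the prescription. The score does not distinguish them.

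This would be mostly noise if both arms had the same information. They do not. The intervention-arm prescriber knows which drug was undetected and holds a conversation meant to end in a tailored plan. The SoC prescriber may also stop drugs, but without knowing which one was absent. The second route is thus open in a targeted way in one arm only, and it pushes the comparison towards the intervention.

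At stake is how a positive adherence result can be read. It could mean that patients take more of their drugs, or that the list was shortened to what they already took.

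**Working it through.** **1. The plan's own figures (Sample size calculation).** Non-adherence at randomisation is assumed to be 50%, falling by a relative 40% (intervention) and 20% (SoC):

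- intervention: 0.50 × (1 − 0.40) = 0.30
- SoC: 0.50 × (1 − 0.20) = 0.40
- implied difference in non-adherence at 12 months: 10 points

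The 196 per arm is for RH prevalence of 80% versus 90%. The unpooled normal formula gives (0.8 × 0.2 + 0.9 × 0.1) × (1.960 + 0.842)² / 0.10² = 196.2, which agrees. That figure is not in dispute and is used below only as the number per arm.

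**2. One patient.** Three measurable drugs A, B and C are prescribed at t0. A and B are found and C is not, so the patient is partially non-adherent. C is then stopped and not replaced. At t12 the expected drugs are A and B, both are found, and the patient is adherent. The patient takes A and B at both visits, exactly as before. A ratio of found to expected drugs would also move, from 2/3 to 2/2, because its denominator resets too.

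**3. Where the route is closed.**

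- C is replaced by a measurable drug: the new drug becomes expected and must be found.
- The patient is switched to drugs outside the assay: the stated rule leaves only blood pressure in the analysis.
- All expected drugs are absent: stopping one leaves the others absent, and stopping all leaves nothing to score.

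What remains is a partially non-adherent patient, a drug stopped without measurable replacement, and the other measurable drugs found.

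**4. Group level (illustration).** Let true non-adherence at 12 months be 40% in both arms, so that there is no real effect. Let f be the share of intervention-arm non-adherent patients rescored by this route. The documents give no value for f, so it is an assumption. No such rescoring is assumed under SoC; if some happens there by chance, read f as the excess over SoC.

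Apparent intervention-arm non-adherence is p₁ = 0.40 × (1 − f), against p₂ = 0.40. With n = 196 per arm and p̄ = (p₁ + p₂)/2:

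- SE₀ = √(2p̄(1 − p̄)/n)
- SE₁ = √((p₁(1 − p₁) + p₂(1 − p₂))/n)
- chance of p < 0.05 = Φ((d − 1.96 SE₀)/SE₁) + Φ((−d − 1.96 SE₀)/SE₁), with d = p₂ − p₁

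| f | p₁ | apparent difference | patients (of 196) | chance of p < 0.05 |
|---|---|---|---|---|
| 0 | 40% | 0 | 0 | 5.0% |
| 5% | 38% | 2 points | 3.9 | 6.9% |
| 10% | 36% | 4 points | 7.8 | 12.9% |
| 20% | 32% | 8 points | 15.7 | 37.8% |
| 25% | 30% | 10 points | 19.6 | 54.6% |

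For f = 25%: p̄ = 0.35, SE₀ = √(2 × 0.35 × 0.65/196) = 0.0482 and SE₁ = √((0.21 + 0.24)/196) = 0.0479. Then (0.10 − 0.0944)/0.0479 = 0.116 and Φ = 0.546; the other tail is negligible. At that value the rescoring alone produces the whole 30% versus 40% contrast that the plan expects.

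**The case against.** The strongest reply is that adherence means taking drugs as prescribed. A regimen that the patient actually takes is then adherence reached from the prescription side, and a tailored solution agreed in the conversation is part of the intervention. On that view the effect of assignment properly includes it. This stands as a defence of the stated class, and is why the class should not be replaced. It does not stand as a reason to leave the two routes unseparated, since the stated aim is to improve adherence through feedback and only one route changes what the patient takes.

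Other parts of the reply also hold:

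- The text does not say that the list is the one at each visit. That is an inference, though a natural one: scoring is done per visit, no baseline list is fixed, and the rule on switching makes measurability follow the changed regimen.
- The endpoint is secondary. Regimen changes are recorded, and the number of drugs and the defined daily dose are compared at t0 and t12, so widespread stopping would show. It would show only at group level, not linked to the adherence score.
- The rescoring rate is assumed.

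Two stronger readings are tempting. A reader might infer that the trial's main result is biased, or that its causal claim fails, because the Abstract ties the fall in RH to increased adherence. The Primary objective section compares RH prevalence between arms without that link, no mediation analysis is described, and the adherence class does not enter the RH definition. A reader might also apply the rate to the full 50% at t0 and obtain 0.50 × 0.10 = 5 or 0.50 × 0.20 = 10 points. These are upper figures: the plan expects a fifth of such patients to improve under SoC, which leaves 40% and hence 4 or 8 points. The 50% also includes fully non-adherent patients, who cannot be rescored by stopping one drug.

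**Conclusion.** The point holds as a possible bias in a secondary comparison, in favour of the intervention. It rests on reading the expected-drug list as the one prescribed at each visit, and on some undetected drugs being stopped without measurable replacement in partially non-adherent patients. The documents permit this and do not say how often it would occur.

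The illustrated shift is 4, 8 or 10 points at rescoring rates of 10%, 20% or 25%, against the 10 points implied by the plan. These figures show that a moderate rate would matter; they do not estimate what will happen. The scoring rule does not affect the primary RH endpoint. Nothing here implies that stopping a drug is right or wrong: the issue is only how the resulting score is read.

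**What to change.** Keep the stated adherence class as the endpoint, and say explicitly which visit's prescription defines the expected drugs. Then:

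1. Prespecify a supplementary between-arm analysis of the proportion adherent. Patients who are adherent only because a drug undetected at any earlier visit (t0, t3 or t6) was stopped without a measurable replacement are not counted as improved. Using t0 alone would miss drugs first undetected later, when intervention-arm providers still receive results.
2. Report the number of such patients by arm.
3. If a per-patient ratio of drugs found to drugs expected is added, report its numerator and denominator by arm, because the denominator also falls when a drug is stopped.

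The per-drug blood spot results and the registered regimen changes already supply the data. No visit, measurement or treatment changes. The cost is a short addition to the plan, a little extra analysis, and possibly a smaller apparent gain in adherence.

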#### Questionnaires

At t = 0 months and t = 12 months patients are asked to fill-in 4 questionnaires. These questionnaires are send either by e-mail or, when requested, by mail. These questionnaires include the beliefs about medicine questionnaire (BMQ), EuroQol-5D-5L (EQ-5D-5L) to determine health-related quality of life, iMTA productivity cost questionnaire (PCQ) and medical consumption questionnaire (MCQ) for economic evaluation which are adjusted for use in our trial [30–32].

Finally, at 12 months follow-up patients are asked to fill in an evaluation questionnaire with regard to the overall experience of the trial.

#### Other study parameters and assessments

At t0 and t12 patient measurement values and available laboratory values are collected (Additional file 1: Table S1). This includes relevant comorbidities, mainly related to cardiovascular diseases, which are derived from the patient record system. Furthermore, serious adverse events (SAEs) are registered troughout the trial up and till four weeks after the last measurement (Additional file 1: Table S1). SAEs are actively reported to the coordinating researcher. Adverse events related to blood pressure are collected from the patient record system.

### Study endpoints

#### Primary objective

Our primary objective is to determine whether an intervention that consists of monitoring AHD concentrations combined with personalised feedback added to SoC leads to a larger decrease in the prevalence of RH after 12 months of follow-up than SoC alone.

#### Secondary objectives

Secondary endpoints include the effect of the intervention on the proportion of patients adherent to AHDs and patients fulfilling the definition of RH over time including baseline (t0), t3, t6 and t12.

Furthermore, the number of required AHDs as well as the defined daily dose (DDD) is calculated at t0 and t12 in both arms to determine if there is a difference over time between the arms.

Lastly, the cost-utility of the intervention vs standard of care in resistant hypertension is determined.

### Data analysis

#### Sample size calculation

The sample size calculation is based on the expected improvements in the prevalence of RH due to improvements in adherence. It is assumed that around 50% of eligible patients is (partially) non-adherent at the moment of randomisation. Based on several adherence trials, we expect a decrease of non-adherence by a relative 40% and 20% in those assigned to the intervention + SoC and SoC alone, and, hence, the expected prevalence of RH at 12 months is expected to be 80% (intervention + SoC) and 90% (SoC alone), respectively [33–35] . A total of 2*196 = 392 patients is required after 12 months of follow-up to demonstrate this difference with β = 0.8 (power = 80%) and a two-sided α = 0.05.

#### Interim analysis

An interim analysis will be performed with data from the trial to check the assumptions made in the sample size calculation. For this at least 25 patients have to be included in both arms that reached three months follow-up. We expect to find a larger differerence at this time point due to the shorter follow-up time, as compared to results after 12 months follow-up when the effect of the intervention is expected to be slightly waned of.

#### Statistical analysis

Continous variables with a normal distribution are described as mean value ± one standard deviation (SD), and otherwise as median value (25th–75th percentile). Normality is tested by the Shapiro–Wilk test. Categorical variables are described as numbers and percentages. Within group changes in percentage non-adherence and RH from t0 to t12 are evaluated by McNemar tests. We use a Chi^2^-test to study change-differences in non-adherence and RH between patients randomised to the intervention + SoC versus SoC alone.

The defined daily dose (DDD) is the assumed average maintenance dose of a drug used for its main indication in adults [36]. These averages are used to determine how many times the DDD for each individual drug is used. Subsequently, the averages of these DDDs are calculated for t0 and t12 for individual patients.

Differences in blood pressure and DDDs over time within the same arm are tested by means of a paired sample t-test and differences between patients randomised to the intervention + SoC versus SoC alone with a independent samples t-test.

We will perform an intention-to-treat analysis, including all randomised patients, as well as a per-protocol analysis, including the patients with available measurements at t0 and t12, and one of t3 and t6.

Data from the questionnaires are used for the cost-effectiveness and cost-utility analysis of the intervention. A cost-utility analysis will be performed with quality adjusted life years (QALY) for a lifelong period. The QALYs will be calculated based on the EQ-5D-5L summary score. Cost-effectiveness from a healthcare perspective will be calculated for a 1-year period using the number of patients fulfilling the definition of resistant hypertension after 12 months (the primary outcome measure).

All p-values are two-sided, and a value of < 0.05 is considered statistically significant.

We used the SPSS version 24.0 for Windows (IBM Corp, Armonk, NY), and GraphPad Prism 9.3 software (GraphPad Software, La Jolla, CA) for analysis.

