### Study design

Eligible patients are informed about the trial by the treating physician. Patients are told that with the fingerprick drug concentrations in blood are measured. However, the term adherence will not be mentioned to the patients and is not included in the patient information leaflet. If the patient is interested in participation, written information will be provided. After at least one week the patient is called by the researchers, to answer patients’ questions regarding study participation. When verbal consent is given, an eligibility visit is scheduled. At this eligibility visit, called t0, written informed consent will be obtained, a 24-h ABPM is performed and simultaneously a finger prick for therapeutic drug monitoring (TDM) is performed. Medication is not standardised prior to inclusion.

Based on the results of the 24-h ABPM during t0, patients are either excluded or randomised to a ‘personalised feedback conversation’ (intervention) added to standard of care (SoC) or SoC alone (Fig. 1).

After randomisation the treating physician is asked to estimate if the patient was adherent to AHDs or not, to determine if there is any bias in selecting patients. The selection of patients is based on blood pressure and thereby resistant hypertension, but physicians can potentially approach only patients they expected to be non-adherent. The adherence estimation is always performed before outcomes on non-adherence are reported (applicable for the intervention + SoC arm).

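### The between-arm tests use neither the randomisation strata nor the t0 values, which costs the RH comparison at most about 8 points of power, and the within-arm McNemar test of RH is uninformative

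*Protocol article*

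**What the plan says.** Under Randomisation, the protocol article divides the hospitals into strata and states: "For each stratum random block randomisation is performed". Under Study design, at the eligibility visit t0 "a 24-h ABPM is performed and simultaneously a finger prick for therapeutic drug monitoring (TDM) is performed", so BP and the adherence sample are obtained from every patient before allocation.

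Under Statistical analysis, the between-arm test for RH and non-adherence is a chi-square test "to study change-differences in non-adherence and RH between patients randomised to the intervention + SoC versus SoC alone". BP and DDD are compared between arms by an independent-samples t-test. No stratum or covariate is named for any of these.

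The same section adds within-arm tests. For the binary outcomes: "Within group changes in percentage non-adherence and RH from t0 to t12 are evaluated by McNemar tests". For the continuous ones: "Differences in blood pressure and DDDs over time within the same arm are tested by means of a paired sample t-test". One significance rule covers all of them: "All p-values are two-sided, and a value of < 0.05 is considered statistically significant".

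Under Sample size calculation, "the expected prevalence of RH at 12 months is expected to be 80% (intervention + SoC) and 90% (SoC alone), respectively", and 196 patients per arm are required "to demonstrate this difference with β = 0.8 (power = 80%) and a two-sided α = 0.05" (0.8 is the power; the β label is a slip).

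**The concern.** There are two separate points.

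**Unused baseline information.** The sample size rationale has RH fall because adherence improves. A patient who already takes all drugs at t0 then has little to gain, so t0 adherence should predict t12 RH strongly. A test that ignores it carries avoidable variance, and the sample size leaves no margin above 80% power. The t-tests likewise do not adjust for the t0 value, and the strata used to randomise do not appear in the analysis.

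**Within-arm test of RH.** Only patients with daytime BP above the cut-off are randomised, so RH is about 100% at t0 in both arms and nobody can move from no RH to RH. A small p-value in either arm shows only that some patients crossed the line. Regression to the mean, unrestricted drug changes and lifestyle changes can all contribute to that. With every p < 0.05 called significant, the test invites a claim of benefit in each arm that the design cannot support.

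**Working it through.** **Inputs from the Sample size calculation section:** RH at 12 months 80% vs 90%; 196 per arm; two-sided α = 0.05; power 80%; 50% (partially) non-adherent at randomisation; relative falls in non-adherence of 40% and 20%.

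**1. The plan's own figure.** With unpooled variance, n = (1.96 + 0.8416)² × (0.8×0.2 + 0.9×0.1) / 0.1² = 7.849 × 0.25 / 0.01 = 196.2 per arm. The stated 196 reproduces (199 with pooled variance).

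**2. What the planning model implies by t0 adherence.** 50% × 40% = 20 points and 50% × 20% = 10 points, which gives 80% and 90%. So RH at t12 is 60% vs 80% in t0 non-adherent patients and 100% vs 100% in t0 adherent patients. The 100% is inferred from the arithmetic; the protocol does not state it.

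**3. Power with and without t0 adherence, 196 per arm (98 non-adherent).**
- Unadjusted: SE = √(0.25/196) = 0.0357; z = 0.1/0.0357 = 2.80; power = Φ(2.80 − 1.96) = 80.0%.
- Stratified: SE = √[0.25 × (0.6×0.4 + 0.8×0.2)/98] = 0.0319; z = 3.13; power = Φ(3.13 − 1.96) = 87.9%.
- Pooled-variance formula: 79.4% to 86.9%.
- Simulation of 200,000 trials, Pearson chi-square against Cochran-Mantel-Haenszel (CMH): 80.1% to 87.0%. Type I error under the null is 4.9% and 5.0%, so both tests are valid.

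**4. Sensitivity.** Keep the 80%/90% margins and let some t0-adherent patients lose RH equally in both arms (simulated):

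| t0-adherent patients who keep RH | Chi-square | CMH | Gain (points) |
|---|---|---|---|
| 100% | 80.1% | 87.0% | 6.9 |
| 98% | 80.2% | 85.1% | 4.9 |
| 95% | 80.1% | 82.8% | 2.7 |
| 92% | 80.2% | 81.4% | 1.2 |
| 90% | 80.2% | 80.7% | 0.5 |

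If the effect is the same in adherent and non-adherent patients, the gain is zero. If instead 10% of everyone becomes controlled in addition (RH 72% vs 81%), the unpooled formula gives 56% rising to 61%.

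The gain also depends on the 50%. With the relative falls kept, simulated power goes from 68.8% to 78.5% if 40% are non-adherent at t0, and from 88.0% to 92.3% if 60% are.

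**5. BP and DDD.** The protocol gives no SD, effect or t0-t12 correlation r, so no power loss can be derived. As an assumption, take equal variances at t0 and t12. ANCOVA variance divided by change-score variance is (1 − r²)/[2(1 − r)] = (1 + r)/2, which is 0.65, 0.75 and 0.85 at r = 0.3, 0.5 and 0.7, or 35%, 25% and 15% lower. If the change-score test had 80% power, ANCOVA would have 94%, 90% and 86%.

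**6. McNemar on RH.** All discordant pairs run one way, so the exact two-sided p is 2 × 0.5^c for c patients leaving RH: c = 5 gives 0.0625 and c = 6 gives 0.031. The planned SoC rate of 10% means about 20 of 196, and 2 × 0.5^20 ≈ 2 × 10⁻⁶. The chance of at least 6 of 196 is 99.99% at a 10% rate, 93% at 5% and 54% at 3%.

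**The case against.** The unadjusted chi-square is a valid, prespecified test that matches the sample size method, and covariates are often left to a statistical analysis plan, which is not shown. This stands: what is lost is efficiency, and nothing is biased. But the article names specific tests, and an analysis plan that follows them inherits the loss.

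The gain of up to 8 points needs every t0-adherent patient to keep RH. That sits badly with the second half of this point, where repeat-measurement noise moves patients out of RH whatever their adherence. The protocol also allows free drug and lifestyle changes in both arms. Its Discussion concedes that some drugs in use cannot be measured, so t0 adherence is partly misclassified. All of this stands and is why the figure is an upper bound.

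A reader might infer that ignoring the strata and t0 BP, or using t-tests, also costs about 8 points. The documents do not support that: the figure comes from one covariate in one comparison. The protocol does not say whether the t-test uses change or t12 values, and a change score already uses t0 BP, though less efficiently than ANCOVA. BP as a continuous variable is not a listed primary or secondary endpoint.

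On McNemar, the primary objective is a between-arm comparison with its own test, and nowhere is the within-arm test said to establish efficacy. That is fair, and it limits the harm to misreading.

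**Conclusion.** The point holds as one of efficiency and interpretation. At the plan's 50% non-adherence and 80%/90% margins, stratifying the RH comparison by t0 adherence adds at most 7 to 8 points of power. The gain is about 5, 3 and 0.5 points if 2%, 5% and 10% of t0-adherent patients become controlled. For hospital strata, t0 BP and the t-tests the case is one of principle, with a range for BP only under an assumed r.

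The within-arm McNemar test of RH says nothing about the intervention. A reader might conclude that it must reject by construction, or that regression to the mean alone will make both arms significant. Neither follows: about 6 of 196 patients have to become controlled, and the protocol gives no estimate of regression to the mean. The 10% SoC rate is its adherence-driven expectation. Rejection is near-certain at the planned rates, not guaranteed. Nor does the one-way argument extend to non-adherence, where patients can move in both directions, or to DDD, which has no entry cut-off that selects high values.

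**What to change.** - **RH at t12:** Mantel-Haenszel or logistic regression, reported as a standardised risk difference with 95% CI and adjusted for randomisation stratum (pooled if sparse), t0 adherence and t0 daytime SBP. Keep the crude chi-square as a sensitivity analysis.
- **Adherence at t12:** the same approach, adjusted for stratum and t0 adherence.
- **BP and DDD:** ANCOVA on the t0 value plus stratum.
- **Within-arm tests:** drop the McNemar test of RH or label it descriptive. Treat the McNemar test of non-adherence and the paired t-tests as descriptive too, not as evidence of an intervention effect.

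The cost is wording in the analysis section and slightly more analysis work; every covariate is already collected. Small hospital strata may need pooling by a rule fixed in advance. Two practical choices should also be fixed beforehand. Mantel-Haenszel can take t0 SBP only in bands. A logistic model may fail to converge if nearly all t0-adherent patients keep RH, as the planning model supposes.
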